**Methods:**

The trial is academically driven and funded by external and hospital research funds. Young, healthy elite boxers aged ≥18 years are recruited. Before, and immediately after a competitive boxing bout consisting of 2 or 3 rounds of 2 minutes each, blood samples are drawn. Boxers are randomized to intervention or control management by 1:1 allocation before baseline testing. After the initial postfight blood sample is drawn and symptom rating using the Sports Concussion Assessment Tool-5 (SCAT-5) has been collected, the boxers receive either acute selective head-and-neck cooling for 45 minutes or routine postfight management. The number of head impacts is counted in all boxers on match video recordings. In both groups, blood samples are drawn 45 minutes after the initial postbout blood sample, as well as 3 and 6 days post fight. At all blood sampling time points, the number of symptoms (NOS) and symptom severity score (SSS) are assessed using the symptom rating part of the SCAT-5. The primary endpoint is the difference in biomarker levels (GFAP, NFL, tau, UCH-L1, neuronal-specific enolase) immediately post fight and preintervention, to those obtained at 6 days post fight. The postfight SCAT-5 NOS and SSS are secondary endpoints.

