#### Study Objectives

The primary objective was to determine whether selective head-and-neck cooling attenuates the concentration of brain injury biomarkers.

The secondary objectives were as follows:

To determine whether selective head-and-neck cooling improves symptom rating using the Sports Concussion Assessment Tool-5 (SCAT-5).To determine whether any biomarker increase post fight, compared to baseline levels, is associated with the number of head impacts.To determine any adverse event associated with the head-and-neck cooling.

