#### Trial Design

The head-and-neck Cooling of Brain temperature In BOXing (COBIBOX) trial is designed as a randomized, controlled, open, single-center superiority trial with 2 parallel groups and a primary endpoint of biomarker changes during the first 6 postfight days. Clinical secondary outcome assessments of a number of symptoms (NOS) and symptom severity score (SSS) using the symptom rating part of the SCAT-5 is performed during the initial 6 postinjury days. Randomization will be performed in blocks with 1:1 allocation.

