#### Procedures and Measurements

All boxing clubs are thoroughly informed of the protocol before study initiation and before each tournament. Boxers between the ages of 18 and 40 years are included. At each tournament, allocation to the treatment takes place on the first morning, and the boxers are randomized 1:1 by a randomly drawn paper slip with a sign that the boxer will receive either selective head-and-neck cooling or routine postfight medical surveillance by an on-site physician. The selective head-and-neck cooling is to be initiated within 10 minutes post fight with a duration of a minimum of 45 minutes. After the boxer completes the fight (Figures 1 and 2), he or she follows the researcher to the cooling station and continues the head-and-neck cooling protocol. In some boxing events, a boxer may participate in two bouts if they win their first bout (Figure 2). The next day, during the finals, they will undergo the same protocol as on their first day, including SCAT-5 assessments and blood sample collection [21]. As mentioned in Figure 2, the start of intervention or return to play protocol starts after their last fight.

Participants will be randomly allocated to either the control or intervention group, involving selective head-and-neck cooling. Baseline SCAT-5 and blood samples will be collected. Subsequently, postfight SCAT-5 and blood samples will be collected for both groups. In addition, the intervention group will undergo selective head-and-neck cooling for 45 minutes. Following this, both the control and intervention groups will follow the same protocol, undergoing SCAT-5 and blood sample collection at 45 minutes post fight, as well as on day 3 and day 6 for follow-up (Figure 1).

The selective head-and-neck cooling takes place after the last boxing bout (dark-colored boxes). For a boxer who fights bout 2/2, new baseline SCAT 5 and blood samples will be collected, shown as baseline 2.0 in Figure 2.

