**Figure 2 figure2:**
[figure not shown]
Boxers who participate in tournaments can either fight one or two boxing bouts, depends on whether they win or lose. SCAT-5: Sports Concussion Assessment Tool-5.

The PolarCap System consists of a portable cooling system, designed to reduce brain temperature by controlled cooling of the scalp and neck with a circulating coolant (PolarCap Coolant, PolarCool AB). The coolant is maintained at 0 °C and flows through a silicone-based head cap. An insulating neoprene cover is put on top of the cap for isolation. The players are allowed to relax (sitting or supine) as long as the cooling head cap and neoprene cover remain in place on the head [22] Should the boxer experience discomfort and wish to discontinue the intervention, the cap is removed and the athlete is excluded from the study. All boxers follow the return-to-fight protocol. The standardized protocol is to return to physical exercise during the first 6 postfight days. During this time, the boxer may do all forms of physical exercise except sparring, match fight, or other activities resulting in impacts to the head or body (Figure 3).

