### Adverse Events

Any adverse events reported by the participant during the study period are noted and reported. Specifically, any deviation from the protocol (eg, sample time point, duration of head-and-neck cooling) will be noted. Symptoms, such as headache, nausea, and dizziness, are reported to the medical doctor and study researcher ([name]), although these symptoms may also be caused by the SRC per se [15]. No adverse events are expected, based on our previous study where 61 elite ice hockey players were cooled without any reported adverse events [15].

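### Boxers who stop cooling because of discomfort are excluded from the study: a post-randomisation exclusion that can act only in the cooled arm and can bias the day 6 comparison

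*Protocol article*

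**What the plan says.** All references are to the Protocol article.

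- **The rule** (Procedures and Measurements, PolarCap paragraph after Figure 2): "Should the boxer experience discomfort and wish to discontinue the intervention, the cap is removed and the athlete is excluded from the study".
- **Who wears the cap** (Procedures and Measurements): "In addition, the intervention group will undergo selective head-and-neck cooling for 45 minutes". Table 1 likewise assigns cooling to the intervention group alone.
- **When allocation happens** (Abstract, Methods): "Boxers are randomized to intervention or control management by 1:1 allocation before baseline testing". The Allocation section has all allocations final at least 3 hours before the tournament starts. Cooling begins only after the bout, once the first post-fight sample and symptom rating have been taken.
- **Design** (Trial Design): "randomized, controlled, open, single-center superiority trial with 2 parallel groups".
- **Primary endpoint** (Abstract, Methods): biomarker levels compared from "immediately post fight and preintervention, to those obtained at 6 days post fight".
- **Safety objective** (Study Objectives, third secondary objective): "To determine any adverse event associated with the head-and-neck cooling".
- **Safety recording** (Adverse Events): "Any adverse events reported by the participant during the study period are noted and reported". The next sentence adds: "Specifically, any deviation from the protocol (eg, sample time point, duration of head-and-neck cooling) will be noted". The same section accepts that headache, nausea and dizziness may come from the concussion itself.

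Nowhere does the article say that a boxer who stops cooling still gives the later samples or is analysed as randomised.

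**The concern.** The rule treats stopping the device as leaving the trial. A boxer it removes has been randomised, has given the baseline and first post-fight samples, and has begun cooling. No control can meet the condition. The cooled arm then becomes those who tolerated the cap, set against all controls, and randomisation no longer protects that contrast.

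The reason for stopping may be linked to the outcome. On the article's own account, the symptoms that could make a boxer give up may reflect the head impacts that raise the biomarkers. For the secondary endpoints the link would be more direct, because the SCAT-5 number of symptoms and severity score are themselves self-reported symptom ratings. The trial is open and stopping is the boxer's own choice.

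An analysis plan can choose its analysis set, but it cannot recover 45-minute, day 3 and day 6 samples that were never drawn. The matter therefore has to be settled in the protocol.

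There is also a question of safety accounting. Cooling-related adverse events are a secondary objective, yet boxers who could not tolerate cooling leave the study, and the article does not say whether they still count.

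**Working it through.** **1. Is the exclusion post-randomisation and one-sided?** The order is allocation, bout, first post-fight sample, cooling, possible stop, exclusion. Only the intervention group is cooled. So yes on both counts, from the article's own text.

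**2. Does it reach the primary endpoint?** The endpoint needs the day 6 sample. A boxer excluded at the cooling station has the post-fight value but no day 6 value, so no change can be computed.

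**3. The plan's own sample size.** Sample Size and Statistical Power gives 20 per group at power 0.8, raised to 25. The text states no SD and no alpha, and the formula is a figure not shown, so 20 can be neither reproduced nor refuted. Assuming two-sided 5%, the implied standardised difference by the normal approximation is

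d = (1.960 + 0.842) × √(2/20) = 0.886 SD.

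The step to 25 fits 20/(1 − 0.20) = 25, that is, a 20% allowance for all dropouts and missed samples. The finding does not depend on these figures; they only give scale.

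**4. Size of the possible bias (assumptions, not trial data).** Let a fraction f of the cooled arm stop, namely those highest on a latent intolerance score that has correlation ρ with the outcome. With no true effect, the large-sample shift in the cooled mean is

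shift = −ρ × φ(z₁₋f)/(1 − f), in SD units.

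Example: f = 0.20 gives z = 0.842 and φ = 0.280, so φ/(1 − f) = 0.350. The shift is −0.105 at ρ = 0.3 and −0.175 at ρ = 0.5.

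Simulation at the trial's size: normal outcomes, two-sample t-test at 5%, 40,000 runs per setting, f = 5, 10 or 20% rounded to whole boxers.

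| Per arm | Cooled boxers removed | ρ | Shift (SD) | Two-sided error | Part favouring cooling |
|---|---|---|---|---|---|
| 20 | 1 | 0.3 | −0.030 | 5.2% | 3.2% |
| 20 | 1 | 0.5 | −0.048 | 5.4% | 3.6% |
| 20 | 2 | 0.3 | −0.058 | 5.3% | 3.7% |
| 20 | 2 | 0.5 | −0.091 | 6.2% | 4.8% |
| 20 | 4 | 0.3 | −0.102 | 6.1% | 4.9% |
| 20 | 4 | 0.5 | −0.165 | 8.0% | 7.3% |
| 25 | 1 | 0.3 | −0.023 | 5.2% | 3.1% |
| 25 | 1 | 0.5 | −0.042 | 5.5% | 3.6% |
| 25 | 2 | 0.3 | −0.044 | 5.3% | 3.7% |
| 25 | 2 | 0.5 | −0.077 | 6.2% | 4.7% |
| 25 | 5 | 0.3 | −0.100 | 6.3% | 5.2% |
| 25 | 5 | 0.5 | −0.167 | 9.0% | 8.4% |

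At ρ = 0 the shift is zero within simulation error and the error rate is 4.8 to 5.1%. With all randomised boxers kept, it is 4.8 to 5.1% in every setting.

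**5. Scale.** Against the implied 0.886 SD, the shifts run from 0.023/0.886 = 3% to 0.167/0.886 = 19%.

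**6. The safety passages side by side.** The Adverse Events section has reported events and deviations in cooling duration noted. The PolarCap paragraph excludes the boxer. These can coexist if the stop is recorded and the boxer then leaves, but the article does not say so, nor whether that boxer enters the adverse-event summary.

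**The case against.** The best defence is that the harm is unproven and probably small.

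- **No bias without a link.** If stopping is unrelated to outcome and response, the rule costs only numbers. This stands: the rule can bias the comparison, and it is not shown that it does. The direction is also assumed. The simulation takes intolerant boxers to have the higher biomarkers; with the opposite sign the bias would run against cooling.
- **No stopping rate.** The article cites 61 cooled ice hockey players without reported adverse events. That is not a discontinuation rate, but it lends no support to a high one. The departures described in Results are three boxers whose opponents dropped out and one who chose to withdraw after the bout with nausea and vomiting. Neither is a stop for cap discomfort, and Figure 4 is not shown. This stands, and it argues for reading the lower rows of step 4 first.
- **Change score.** The primary endpoint is a change from the post-fight sample, so severity already visible in that sample is partly removed. This stands in part: ρ must be read as the correlation with the change, and a link with the later course remains possible.
- **Exploratory aim.** The Discussion calls the study explorative. That lowers the stakes but does not justify a one-sided exclusion.

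A reader might also infer that the rule wipes out the trial's intolerance data, or that adverse-event rates are bound to be understated. The article does not support this. Discomfort that ends cooling occurs before the exclusion, and the Adverse Events section has both reported events and shortened cooling noted. Nor does noting a short duration necessarily imply that the boxer stays in, so the passages are unclear together rather than flatly contradictory.

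**Conclusion.** The point holds in a limited form. The article fixes a post-randomisation exclusion that can act only in the cooled arm, and nothing in it keeps these boxers in the day 6 comparison. The rule can bias the biomarker and SCAT-5 comparisons if stopping is related to severity or response. It also ends later sampling, symptom rating and adverse-event follow-up, and it leaves the boxer's place in the safety summary unclear.

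Under the assumptions in step 4 (no true effect, 20 to 25 per arm, 5 to 20% stopping, ρ from 0.3 to 0.5), the shift is about −0.02 to −0.17 SD and the two-sided error about 5 to 9%. An error near 16% can be produced, but it needs five of 25 cooled boxers to stop and a correlation of 0.8, and the documents support neither. A 20% stopping rate alone would use up the whole implied allowance for losses in that arm.

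This should be fixed. It is not a fatal flaw: the number affected is unknown and the plausible bias is modest beside the difference the trial is sized to detect.

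**What to change.** Leave the rule on removing the cap as it is and change only the closing clause of that sentence. It should say that, unless the boxer withdraws consent, he or she stays in follow-up (45-minute, day 3 and day 6 samples and SCAT-5) and is analysed in the allocated arm.

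In addition:

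- Report the number of, and reasons for, stops due to discomfort in the cooled arm, and state that these boxers count towards the adverse-event objective. This reconciles Study Objectives, the PolarCap paragraph and Adverse Events.
- Show an analysis restricted to boxers who completed 45 minutes only as a sensitivity analysis.
- If any boxer has already been excluded under this rule, report that and include the data available. The day 6 value may be missing for such a boxer.

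The cost is one sentence and no new visits, since the samples and ratings are already scheduled. Keeping incompletely cooled boxers may dilute the effect estimate slightly. The boxer's right to stop cooling or to leave the study is unchanged.

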**Figure 3 figure3:**
[figure not shown]
(A) The PolarCap unit is a powerful mobile cooling system. (B) The Polar Coolant is transported through the silicone head cap. (C) To insulate against the cold, a neoprene cover is applied on top of the cap.

Blood samples are collected at the following time points for all participants: the morning of the first boxing fight on day 1 (baseline, at rest), immediately after the fight, 45 minutes after the fight, and after 3 and 6 days in all boxers. The blood samples obtained at 3 and 6 days post fight will be drawn by a study nurse or a researcher ([name]) at the participants’ boxing club. The samples are transported to the hospital in a mobile refrigerator to maintain a temperature of 5-8 °C. Thereafter the serum samples are centrifuged at 3000 rpm, at 4 °C for 10 minutes, after which 800-1200 µL is transferred using a pipet to 2-mL tubes and stored at –80 °C.

At each time point for blood sample collection, boxers are also administered the SCAT-5 questionnaire, which is a self-report questionnaire with information on 22 different symptoms, each with a severity grading of 0-6, where 0 indicates no symptoms and 5-6 indicates severe symptoms. The maximum total score is 132. All boxing bouts are video-recorded for later analysis. The total hits per bout, strikes to the head, strikes to the body, and visible evidence of neurological disturbance (loss of consciousness, impaired balance or coordination, vacant expression, etc) will be assessed. After completion of the study, the boxers will be interviewed by phone to answer questions about their previous boxing, knock-out, and concussion history. The timeline for enrollment intervention and assessments across the study is visualized in Table 1 (SPIRIT [Standard Protocol Items: Recommendations for Interventional Trials] checklist in Multimedia Appendix 1).

**Table 1 table1:** Timeline of enrollment, intervention, and assessment during the study period.

Procedures		Study period				Post allocation						Close-out
		Enrollment	Preallocation	Allocation								
Time point		–t_1_	Baseline	0	Post fight		45 min post fight	Day 3	Day 6	1 week post fight		
**Enrollment**		✓										
	Eligibility screen	✓										
	Informed consent	✓										
	Basic medical examination	✓										
	Allocation			✓								
**Interventions**												
	Selective head and neck cooling (A^a^)				✓							
	Return to fight protocol (A+B^b^)				✓		✓	✓	✓			
	Collecting blood sample		✓		✓		✓	✓	✓			
**Assessments (SCAT-5^c^)**												
	SCAT-5		✓									
	SCAT-5 follow-up				✓		✓	✓	✓			
	Boxing history									✓		

^a^A: intervention group.

^b^B: control group.

^c^SCAT-5: Sport Concussion Assessment Tool-5.

### Ethical Considerations

The study outlined in this article will be carried out in accordance with the Declaration of Helsinki. Regional ethics committee approval in Lund, Sweden (decision number Dnr 2022/06195) was obtained. Before their enrollment in the trial, all study participants will provide written informed consent. Each participant signs the form, containing comprehensive study details. Approval from the Swedish Boxing Association to include amateur and professional boxers registered in the Swedish Boxing Association (SBA) in the study will be received before the study is initiated. Forms describing the study are sent to all boxing clubs in southern Sweden that would participate in the tournaments and have enrolled boxers over 18 years old. All participants are informed of their right to terminate their participation in the study at any given time without the need to provide a reason for doing so. All questionnaires and data collection methods were reviewed and approved by the Swedish Ethical Review Authority in Uppsala, Sweden. The submitted protocol to the Swedish Ethical Review Authority included detailed information on the intervention, data confidentiality, blood collection, blood sample storage, and measures to ensure the protection of participants’ privacy. A study protocol was provided with the ethical application. All participants' data are anonymized from the time of inclusion, before allocation, by assigning a code containing letters and numbers. This code will be attached to the participants’ blood samples and SCAT-5 score files. Each participant will receive a compensation of 1000 SEK (US $104.53) for their time, inconvenience, and any potential discomfort associated with participation. The consent information emphasizes the voluntary nature of participation, including the possibility of opting out at any stage. It also specifies who will obtain informed consent from the participants. Specific contact information for the research team is provided to participants for any questions or concerns. The informed consent consists of 10 detailed points. It begins with a request for participation that describes what the boxers will be involved in. The background and aim section explains the purpose of the study and the facts supporting it. The study procedure outlines the collection of SCAT-5 questionnaires, blood samples, and the possibility of cooling. Biomarker collection is covered by the biobank policies and includes the category of biomarkers that will be analyzed. The risk section highlights any potential risks associated with participation. Handling personal data explains data protection measures in accordance with GDPR, while data management and privacy further detail how data are stored and covered under GDPR. The insurance section clarifies the responsible parts that ensure the participants during the study. Voluntary participation ensures that participants are informed of their right to opt out at any time, even after inclusion. Finally, the responsible staff section provides information about the staff in charge and their contact details.

### Study Population

A total of 14 boxing clubs whose fighters enrolled in 5-7 boxing events in southern Sweden will be contacted and informed about the study and its inclusion criteria.

### Allocation

After all boxers have approved participation in the study during the tournament, and signed the informed consent, the study staff makes an allocation on paper slips that equals the number of participants. Then the boxers randomly, by drawing a paper slip, receive either a sign for receiving head-and-neck cooling (C=cooling) or NC (no cooling; Figures 1-2). All allocations are finalized a minimum of 3 hours before the start of the tournaments.

The enrollment of participants will be done by a researcher ([name]) aided by boxing coaches.

After the boxing bout, and after the boxer is evaluated for red flags mandating transport to the nearest hospital, the boxer is brought to the intervention station to apply the PolarCap system as previously described.

### Personnel Responsible for Informed Consent

Informed consent documents will be sent for approval to the Swedish Boxing Association, after which those will be distributed to each club. A responsible researcher and physician ([name]) will inform the participants verbally and in written form, either days before the competition or on the same day. Each participant will be informed about the study, informed of the possibility to withdraw from participation at any time, and provided time to ask questions. Before randomization, each participant signs the informed consent form.

### Biomarker Analysis

Venous blood is collected in 3.5 mL serum and EDTA plasma tubes generated at room temperature and stored in a mobile refrigerator at 4-8 ºC until centrifuged at 4 ºC for 10 minutes at 3000 rpm. The remaining supernatant is transferred to 2 mL cryotubes and stored at –80 ^o^C until analyzed. Once the study has been completed, blood biomarkers for brain injury (S100B, GFAP, tau forms, NFL, and NSE) will be measured in coded samples using an established single-molecule array (for GFAP, tau, and NFL) by Quanterix and electrochemiluminescence immunoassays (for S100B and NSE) by Roche Diagnostics immunoassays [23] in the Clinical Neurochemistry Laboratory by board-certified laboratory technicians who will be blinded to the intervention.

